### 5.4. Baseline Characteristics

The following baseline characteristics will be collected: age, sex, preoperative estimated glomerular filtration rate (eGFR in mL/min/1.73 m^2^), preoperative hemoglobin (Hb in mmol/L), preoperative hematocrit (Ht in L/L), type of DOAC (apixaban, edoxaban, rivaroxaban, or dabigatran), DOAC dosage, DOAC indication, hours since last DOAC intake, concurrent use of antiplatelet medication (yes/no), and the specific type of concurrent antiplatelet or anticoagulant medication used. Frailty indicators include a prior diagnosis of dementia (by a geriatrician or general practitioner), Body Mass Index (BMI in kg/m^2^), Short Nutritional Assessment Questionnaire (SNAQ) score, Clinical Frailty Scale (CFS), Charlson Comorbidity Index (CCI), American Society of Anesthesiologists (ASA) score, number of daily medications, pre-fracture living situation (independently at home, with assistance in Activities of Daily Living (ADL), or in institutional care facility), household composition (living alone, with a partner, or with family), pre-fracture mobility (based on the Fracture Mobility Score), and Katz-6 ADL score [47,48,49,50,51,52]. Fracture characteristics include the type of fracture (based on AO/OTA classification) and the surgical procedure performed (hemiarthroplasty, total hip arthroplasty, intramedullary nail, sliding hip screw, or cannulated hip screw) [46]. Lastly, the type of anesthesia (general or spinal), any preoperative use of tranexamic acid, fibrinogen, or platelet concentrates, and DOAC reversal agents (idarucizumab or andexanet alfa) will be registered. In addition, patients whose surgery was delayed for reasons unrelated to DOAC use will be documented, along with the specific reason for the delay. Measurement of DOAC plasma levels is not part of routine care in the participating centers and is therefore not included.

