### 5.7. Sample Size and Rationale for Non-Inferiority

The research question of this study is framed as a non-inferiority comparison, and the sample size has therefore been calculated to test non-inferiority. This study used the most recent institutional data, as these best reflect the clinical context and patient population of this study. These institutional data showed a transfusion rate of approximately 15% in the delayed surgery group and 10% in the early surgery group, which is considered appropriate for powering a non-inferiority analysis in this natural experiment. In consultation with clinical experts, a non-inferiority margin (ΔNI) of 5% is deemed clinically acceptable to conclude that early surgery does not result in a clinically relevant increase in transfusion requirement. Non-inferiority will be demonstrated if the upper bound of the one-sided 95% confidence interval for the absolute risk difference between groups remains below 5%. Based on these assumptions, an expected event rate of 15% in the control group and 10% in the intervention group, with a one-sided alpha of 0.05 (Zα = 1.645) and a power of 90% (Zβ = 1.282), the required total sample size is 374 patients, with 187 per group.

As the sample size is based on the per-protocol population, patient inclusion will continue until 187 patients per treatment group have been included who adhered to the protocol of their respective school of treatment (Figure 2). Inclusion in a given school will stop once the required number of per-protocol patients (*n* = 187) is reached in that group. The other school will continue including patients until it also reaches the target of 187 per-protocol patients. As a result, the intention-to-treat population is expected to exceed 374 patients. Since the primary outcome is assessed during hospitalization, no loss to follow-up is anticipated. This approach provides sufficient power to robustly assess non-inferiority within the specified parameters.

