### 5.8. Statistical Analysis

#### 5.8.1. Primary Outcome

The primary outcome is postoperative blood transfusion in hip fracture patients on DOACs. To assess non-inferiority of early surgery within 24 h compared to delayed surgery 24 h or more after last DOAC intake, the risk difference in transfusion requirement between both groups will be calculated with a corresponding one-sided 95% CI. Non-inferiority will be concluded if the upper bound of the one-sided 95% CI does not exceed the predefined non-inferiority margin of 5%.

In addition, a multivariable logistic regression analysis will be performed to estimate the adjusted odds ratio (aOR) and associated 95% CI for transfusion requirement, adjusting for potential confounders. Based on literature and expert-opinion, the following variables will be considered for inclusion in the regression model: sex, preoperative Hb, Clinical Frailty Scale, and type of surgical procedure [59,60,61,62]. Given a total sample size of 374 and an expected event rate of 15%, approximately 56 events are anticipated, allowing for inclusion of up to five independent variables, in accordance with standard rules to prevent model overfitting.

The primary analysis will follow a per-protocol approach, in which patients will be analyzed based on adherence to the surgical timing protocol of their respective hospital (i.e., within 24 h for School “A” centers and after 24 h or more for School “B” centers). Patients whose surgical timing deviates from this hospital protocol will be identified and excluded from the per-protocol analysis (Figure 2). In addition, an intention-to-treat (ITT) analysis will be conducted, in which patients will be analyzed according to the timing policy of their admitting hospital, regardless of actual timing. This ITT analysis will serve to assess the robustness of the findings, while preserving the effect of quasi-randomization and limiting the risk of confounding by indication. As a sensitivity analysis, propensity score matching will be applied to further assess robustness of the primary findings. This analysis will allow comparison of results obtained using propensity score matching with those derived from the natural experiment design and provide additional insight into the methodological value of the natural experiment approach.

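### The adjusted model is sized on 56 events, but the plan's own rates of 15% and 10% give about 47, which leaves no room for the five terms it allows at ten events each

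*Protocol article*

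**What the plan says.** Section 5.7 (Sample Size and Rationale for Non-Inferiority) takes its rates from institutional data showing "a transfusion rate of approximately 15% in the delayed surgery group and 10% in the early surgery group". It powers the study on "an expected event rate of 15% in the control group and 10% in the intervention group", with a margin of 5 percentage points, one-sided alpha of 0.05 and 90% power, and arrives at 187 per group and 374 in total.

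Section 5.8.1 (Primary Outcome) tests non-inferiority on the risk difference and adds a multivariable logistic regression for an adjusted odds ratio. It sizes that regression as follows: "Given a total sample size of 374 and an expected event rate of 15%, approximately 56 events are anticipated". From this it concludes that up to five independent variables can be included without overfitting. The covariates to be considered are sex, preoperative haemoglobin, the Clinical Frailty Scale (CFS) and type of surgical procedure. Section 5.4 (Baseline Characteristics) records the procedure as "hemiarthroplasty, total hip arthroplasty, intramedullary nail, sliding hip screw, or cannulated hip screw", which is five categories.

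**The concern.** The two sections use different event rates for the same 374 patients. Section 5.7 has a different rate in each group. Section 5.8.1 applies the higher of the two, the delayed-surgery rate, to everyone. The resulting count is not incidental, because it is the only basis given for how many variables the model may carry.

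The adjusted model matters because the comparison is not randomised. Section 1 (Strengths and Limitations) explains that overfitting limits the number of covariates, and relies on the model to account for the most relevant confounders. An overstated event count makes that model look better supported than the planning assumptions allow. Procedure is also hard to leave out: section 5.2.2 describes one hospital where the type of operation determines whether surgery is early or delayed.

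**Working it through.** **Inputs.** From section 5.7: 15% (delayed), 10% (early), 187 per group, margin 0.05, Z values 1.645 and 1.282. From section 5.8.1: 15% of 374, about 56 events, up to five variables, four named covariates. From section 5.4: five procedure categories.

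**1. The sample size reproduces.** With unpooled variance,

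n = [0.15×0.85 + 0.10×0.90] × (1.645 + 1.282)² / (0.05 + 0.05)² = 0.2175 × 8.567 / 0.01 = 186.3, rounded up to 187 per group.

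Power at 187 per group is 90.1%. Section 5.7 is therefore internally sound and does rest on 15% versus 10%.

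**2. The 56 reproduces only with a 15% overall rate.** 374 × 0.15 = 56.1.

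**3. Events under section 5.7.** 187×0.15 + 187×0.10 = 28.05 + 18.70 = 46.75, about 47. The pooled rate is 46.75/374 = 12.5%. The shortfall is 56.1 − 46.75 = 9.35 events, and 9.35/56.1 = 17%. In a simulation of the 15%/10% assumptions, 56 or more events occurred in about 9% of runs, and the central 95% of runs lay between 35 and 60 events.

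**4. The implied rule.** The plan does not name its rule. Five variables from 56.1 events is 11.2 events each, which fits a threshold of ten (56.1/10 = 5.6, rounded down to five). The same threshold with 46.75 events gives 4.7, rounded down to four.

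**5. Terms needed.** Timing group plus sex, haemoglobin, CFS and procedure makes five variables: 46.75/5 = 9.35, about 9.4 events each.

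**6. Parameters, if procedure keeps five levels (an assumption).** Timing 1 + sex 1 + haemoglobin 1 + CFS as a linear term 1 + procedure 4 = 8. Then 46.75/8 = 5.8 events per parameter; even with 56.1 events it would be 7.0.

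**7. A separate sensitivity figure for section 5.7.** Power = Φ((0.05 − (p_early − p_delayed))/SE − 1.645), with 187 per group.

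| Delayed | Early | Overall | Power |
|---|---|---|---|
| 15% | 10% | 12.5% | 90.1% |
| 17.5% | 12.5% | 15% | 85.8% |
| 15% | 15% | 15% | 38.6% |

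For the last row, SE = √(2 × 0.1275/187) = 0.0369. A simulation gave 39.3%. Reaching 90% power at equal 15% rates would take 874 per group.

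**The case against.** The strongest reply is that the slip is small and that little depends on it. Non-inferiority is decided on the risk difference, and the regression is an addition. Section 1 already concedes a limited covariate set and residual confounding, and section 5.8.1 plans propensity score matching as a sensitivity analysis. The plan's rule counts variables rather than parameters: timing plus four covariates is five, which meets the stated limit, and 9.4 events each is only just under ten. The covariates are also only candidates, and their coding may properly be left to an analysis plan that is not shown.

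Most of this stands. It limits the consequence, but it does not remove the contradiction between two stated figures, nor the fact that the incorrect one sets the size of the model.

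Two stronger readings are tempting and should be set aside. A reader might infer that the model is already overfitted by the plan's own rule, at eight parameters. The documents do not say that procedure will enter as four indicators, so the eight is conditional. A reader might also infer that section 5.8.1 puts 15% in both groups and so lowers the study's power to 39%. It gives one overall rate, and an overall 15% is compatible with 17.5% versus 12.5%, where power stays near 86%.

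**Conclusion.** The event count in section 5.8.1 is wrong under the plan's own assumptions: about 47, not 56. This follows directly from section 5.7 and needs no outside input. Given a threshold of about ten events per variable, which is inferred from the plan's figures, the allowance falls from five terms to four, while timing and the listed covariates need five. The shortfall is slight if each variable takes one parameter (9.4 events each) and material if procedure keeps all five categories with CFS linear (5.8 each).

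The calculation of 187 per group is correct, and the primary test does not use the event count. The 39% power at equal 15% rates is arithmetically right, but it is a sensitivity figure for section 5.7. It is not an error there or a consequence of section 5.8.1: section 5.7 states its rates openly and claims power only for them.

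**What to change.** In section 5.8.1, replace 56 with about 47 (12.5% of 374) and restate the allowance as about four to five parameters, counting the timing term. Then hold the model to that number. One way is to code procedure as arthroplasty versus internal fixation, which gives five parameters at 9.4 events each. That is still slightly under ten and should be described as such; it keeps the distinction on which the mixed-protocol hospital's timing depends. Penalised regression is an alternative if finer procedure categories are wanted.

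No patients are added. The count is a change of wording and makes the stated figure less favourable. Fixing the coding or the estimation method is a change to the analysis specification, and collapsing procedure adjusts for it more coarsely.

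Separately, and as an improvement rather than a correction, section 5.7 could qualify its closing claim, "This approach provides sufficient power to robustly assess non-inferiority within the specified parameters". It could say that 90% power depends on early surgery having a transfusion rate 5 points lower, and that power would be about 39% if both rates were 15%.

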## Abstract

**Background**: Early surgical intervention is associated with improved outcomes in hip fracture care, yet in patients using Direct Oral Anticoagulants (DOACs), surgery is frequently delayed due to concerns about increased intraoperative bleeding. Despite the increasing prevalence of hip fracture patients on DOACs, no consensus exists on optimal surgical timing. This has led to substantial practice variation between hospitals, with some operating within 24 h of last DOAC intake and others delaying surgery beyond 24 h. This study hypothesizes that early surgery within 24 h results in a non-inferior blood transfusion risk compared to delayed surgery 24 h or more after last DOAC intake in hip fracture patients on DOACs. This protocol describes the design and methodological rationale of a natural experiment. **Methods and analysis**: A multicenter cohort study designed as a natural experiment will be conducted across seven Dutch level 2 trauma centers, using predefined and standardized prospectively collected variables from electronic health records. Centers will adhere to distinct local surgical timing protocols, forming two cohorts: early surgery within 24 h and delayed surgery 24 h or more after last DOAC intake. Patients presenting with an isolated hip fracture who are using a DOAC and have taken their last dose within 24 h before admission will be included. The primary endpoint is postoperative blood transfusion. Secondary endpoints include additional bleeding-related outcomes, thrombotic and postoperative complications, and hospital length of stay. The primary analysis will be conducted on a per-protocol basis, with an intention-to-treat analysis performed as a supplementary assessment. Non-inferiority will be established if the upper bound of the one-sided 95% confidence interval for the risk difference does not exceed the predefined margin of 5%. **Ethics and dissemination**: Ethical approval was obtained from the Medical Ethics Committee United, Utrecht, The Netherlands. As this is a cohort study without altering clinical care, individual informed consent is not required. All data will be pseudonymized, and findings will be disseminated through peer-reviewed journals and scientific conferences. **Registration details**: Medical Ethics Committee United, Utrecht, The Netherlands, registration number W25.034.

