## 1. Strengths and Limitations

This study addresses an urgent and clinically relevant knowledge gap regarding the optimal surgical timing for hip fracture patients on direct oral anticoagulants, with the potential to improve national and international guidelines.It utilizes a natural experiment design across seven Dutch trauma centers, leveraging existing practice variation to approximate randomization and enable real-world comparison of early surgery within 24 h versus delayed surgery 24 h or more after last direct oral anticoagulant intake, without interfering with routine clinical care, enhancing the generalizability of the findings.While the retrospective data extraction from electronic health records at predefined intervals is a limitation, all variables are prospectively predefined and standardized across participating hospitals, and regular data quality checks with structured feedback to centers are implemented to ensure consistency, completeness, and high data quality.Due to the limited number of covariates allowed in the regression model to prevent overfitting, there remains a risk of residual confounding; however, the most clinically relevant confounders will be accounted for in the analysis.A per-protocol primary analysis may be susceptible to confounding by indication; however, a pre-planned intention-to-treat analysis will assess the robustness of findings and mitigate this bias. In addition, time-dependent confounding cannot be fully excluded. Clinical or logistical factors arising during the preoperative waiting period, such as medical optimization, complications, or operating room availability, may influence both surgical timing and outcomes independent of direct oral anticoagulant status.

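### Non-inferiority is decided on the per-protocol set alone; the ITT analysis, relied on against that set's admitted bias, has no stated effect on the conclusion

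*Protocol article*

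**What the plan says.** The Abstract sets the hierarchy: "The primary analysis will be conducted on a per-protocol basis, with an intention-to-treat analysis performed as a supplementary assessment". Section 5.8.1 handles deviators as follows: "Patients whose surgical timing deviates from this hospital protocol will be identified and excluded from the per-protocol analysis". Section 5.7 sizes the study on the same set, recruiting until each school has 187 adherent patients.

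The decision rule in 5.8.1 is one condition: "Non-inferiority will be concluded if the upper bound of the one-sided 95% CI does not exceed the predefined non-inferiority margin of 5" per cent. The Abstract, 4.1 and 5.7 state the same single condition. None of them names an analysis set. Since the per-protocol analysis is primary, it supplies the bound.

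On ITT, 5.8.1 says "This ITT analysis will serve to assess the robustness of the findings, while preserving the effect of quasi-randomization", and adds that it limits confounding by indication. Section 1 concedes that "A per-protocol primary analysis may be susceptible to confounding by indication" and continues that "a pre-planned intention-to-treat analysis will assess the robustness of findings and mitigate this bias". No section holds ITT to the 5% margin or says how a disagreement between the sets is read.

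**The concern.** The design's credibility rests on patients reaching hospitals of different policy independently of their own characteristics (5.2.1, 5.2.2). Dropping patients by their actual surgical timing sets part of that aside.

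Section 5.3 admits patients whose last dose was up to 24 h before arrival, so some School A patients have little of their window left. Section 1 lists medical optimisation, complications and theatre availability as causes of delay that may also affect outcome. If the School A patients who miss the window are at higher transfusion risk, excluding them lowers the School A rate in the deciding analysis and favours early surgery. ITT keeps them, but under the stated rule its result cannot alter the conclusion.

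At stake is a positive claim that section 3 says would support a major change in practice.

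**Working it through.** **1. The plan's own figure.** Inputs from 5.7: 15% delayed, 10% early, margin 5 points, one-sided alpha 0.05, power 90%.

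n per group = (0.15×0.85 + 0.10×0.90) × (1.645 + 1.282)² / (0.05 + 0.05)² = 186.3, so 187. The stated 374 is reproduced. The sample size is not in error; it is a per-protocol sample size.

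**2. Assumptions.** The article gives neither deviation rates nor transfusion rates in deviators; 5.2.2 calls deviation rare. Throughout: 187 adherent patients per school, 10 School B deviators (5% of 197) transfused at 15%, and School A deviators numbering 10, 21, 33, 47 or 62 (5, 10, 15, 20 or 25%). Bounds are Wald bounds on the risk difference; probabilities come from 400,000 simulated studies.

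**3. One dataset where the sets part** (illustrative counts).
- Per-protocol, 25/187 v 28/187: difference −1.6 points; bound −0.0160 + 1.645 × 0.0361 = +4.3. Non-inferiority is declared.
- Add 33 School A deviators with 10 events and 10 School B deviators with 3 events. ITT, 35/220 v 31/197: difference +0.2; bound 0.0017 + 1.645 × 0.0358 = +6.1. ITT fails the margin.

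**4. False declaration.** Put the true ITT difference at the margin (20% v 15%) with School A deviators transfused at 30%. The adherent School A rate must then be (0.20 × (187 + n) − 0.30 × n)/187. For n = 47 this is (46.8 − 14.1)/187 = 17.5%.

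| School A deviation | Adherent School A rate | Per-protocol rule declares | ITT test passes |
|---|---|---|---|
| 5% | 19.5% | 7% | 5% |
| 10% | 18.9% | 9% | 5% |
| 15% | 18.2% | 12% | 5% |
| 20% | 17.5% | 17% | 5% |
| 25% | 16.7% | 23% | 5% |

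Hand check at 20%: the per-protocol difference is 2.49 points, SE = √(0.1749×0.8251/187 + 0.15×0.85/187) = 0.0381, and Φ((0.05 − 0.0249 − 1.645×0.0381)/0.0381) = Φ(−0.99) ≈ 16%, in line with the simulated 17%. If deviators carry the same 20% risk as everyone else in School A, the per-protocol set is itself at the margin and the rule keeps its nominal 5%. The inflation comes from selection.

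**5. Discordance and joint power at the planned rates** (10% v 15%; per-protocol power about 90.5%).

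| School A deviation | Deviator rate | True ITT difference | Per-protocol passes, ITT fails | Both pass |
|---|---|---|---|---|
| 5% | 15% | −4.7 points | 2% | 89% |
| 5% | 30% | −4.0 | 6% | 84% |
| 10% | 30% | −3.0 | 14% | 76% |
| 20% | 15% | −4.0 | 4% | 86% |
| 20% | 30% | −1.0 | 34% | 57% |

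If deviators do not differ from their own school's adherent patients, joint power is about 89–90%. If deviators in both schools take the other cohort's rate at 20% School A deviation, it is about 86%.

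**The case against.** A per-protocol primary analysis with ITT in support is a recognised choice for non-inferiority, because ITT can be diluted by deviations. That stands; the choice of primary set is not the fault.

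A reader might infer from the 34% in step 5 that a third of studies would reach a false conclusion. The figures do not support this. The true ITT difference there is −1.0 point, well inside the margin, so ITT fails for want of power. That is discordance, not false declaration. The measure of harm is step 4, which is smaller at low deviation.

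The deviation and deviator rates are assumptions. With deviation rare, as 5.2.2 says, the rows at 5% and 10% are the relevant ones. Step 4 also takes the comparison by school policy as the truth; a reader who regards only adherent patients as the target would count fewer of those declarations as errors.

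A reader might also infer that the planned ITT analysis is worthless, or that the article says nothing else preserves the quasi-randomisation. Neither is supported. A reported ITT result shows whether exclusions drive the finding; the article also plans propensity matching and adjusted regression (5.8.1) and records reasons for delays unrelated to DOAC use (5.4). But none of these has a stated part in the decision either.

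Finally, handling of discordance could be left to a fuller plan. The decision rule, however, is stated complete in four places with one condition, so this is a rule as fixed, not a missing detail.

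**Conclusion.** The point holds as a weakness in a stated decision rule. The article admits a bias in the per-protocol set, names ITT as the remedy, and gives ITT no effect on the conclusion. If School A exclusions are selective for higher risk, the rule is anti-conservative: with 30% transfusion in those deviators and 5% deviation in School B, false declaration is about 7–9% at 5–10% School A deviation and reaches 23% at 25%, against 5%. If deviation is rare and deviators resemble the rest, little changes. The documents do not show which case applies, so this is an inexpensive safeguard worth adding, not proof that the study will mislead.

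**What to change.** State in the Abstract, 4.1, 5.7 and 5.8.1 that non-inferiority is concluded only if the one-sided 95% upper bound is below 5% in both the per-protocol and the ITT set, and that discordant results are reported as non-inferiority not established. In section 1, replace the claim that ITT will reduce the bias with a statement of this role.

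Define the ITT set so that it can bear that weight. Section 5.8.1 assigns patients by the policy of the admitting hospital, 5.2.3 moves them between schools by surgeon-level protocol after a policy change, and 5.2.2 includes a hospital whose policy depends on the procedure. These must be reconciled.

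Cost: both analyses are already planned, no new data are needed, and no alpha adjustment arises because both must pass. The price is power. The 90% in 5.7 should be labelled per-protocol power, with joint power given beside it under stated deviation assumptions: about 89–90% if deviators do not differ, and about 84%, 76% or 57% at 5, 10 or 20% School A deviation if those deviators are transfused at 30%.

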## 5. Materials and Methods

### 5.1. Study Design

This cohort study is designed as a natural experiment and includes seven level 2 trauma centers across The Netherlands. Participating hospitals follow either an expert-based protocol permitting surgery within 24 h after the last DOAC intake or a conservative protocol requiring a minimum delay of 24 h. Patient inclusion starts in November 2025 and is expected to conclude in June 2027.

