Lastly, although we do not expect substantial inter-hospital variability, since all participating centers are Dutch level 2 trauma centers with similar hip fracture case volumes and resources, we will assess clustering by center using an intraclass correlation coefficient. If clustering of outcomes is detected (i.e., if some hospitals show greater similarity in outcomes than others), we will perform a multilevel logistic regression analysis to account for center-level effects. If no relevant clustering is found, the standard multivariable logistic regression will be deemed sufficient.

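### Timing is set by hospital policy in seven hospitals, but neither the sample size nor the stated clustering remedy lets hospital variation into the risk-difference interval that decides non-inferiority

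*Protocol article*

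**What the plan says.** Section 5.1 says the study "includes seven level 2 trauma centers across The Netherlands". Section 5.2.2 puts three hospitals in the early school and four in the delayed school, and states that timing is fixed by institutional protocol. One hospital splits by procedure: prosthesis surgery is delayed and all other procedures are early. Section 5.2.3 allows allocation to move to surgeon level after a policy change.

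Section 5.7 assumes "an expected event rate of 15% in the control group and 10% in the intervention group", a margin of 5 percentage points, a one-sided alpha of 0.05 and 90% power. It concludes that "the required total sample size is 374 patients, with 187 per group". It mentions no ICC, design effect or number of hospitals.

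Section 5.8.1 decides non-inferiority on the risk difference between the two groups with a one-sided 95% interval. A logistic regression giving an adjusted odds ratio comes in addition. On clustering, the section says "we will assess clustering by center using an intraclass correlation coefficient". If clustering is detected, a multilevel logistic regression is run. Otherwise, "If no relevant clustering is found, the standard multivariable logistic regression will be deemed sufficient". No threshold or test for detection is given.

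**The concern.** When a whole hospital works to one timing policy, the comparison is largely between groups of hospitals, so differences in transfusion frequency between hospitals are part of its error. With three hospitals against four, those differences cannot be relied on to average out, and more patients in the same hospitals do not remove them.

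The plan leaves this error out in two places. The sample size treats patients as independent. The clustering step depends on what the data show, and it replaces one odds-ratio model with another while the deciding interval stays as it was. An interval that is too narrow makes it easier to declare early surgery non-inferior. That is the unsafe direction for a conclusion that section 3 says would support changing practice.

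**Working it through.** **Inputs from the article.** Event rates 15% (delayed) and 10% (early), margin 0.05, one-sided alpha 0.05 (z = 1.645), power 90% (z = 1.282) and 187 per group, all from 5.7. Three and four hospitals, from 5.2.2.

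**Assumed.** ICCs of 0, 0.005, 0.01, 0.02 and 0.05, because the article gives none. Hospitals are of equal size within each school: 187/3 = 62.3 and 187/4 = 46.75 patients. The mixed-protocol hospital and any policy switch are ignored.

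**Step 1: the plan's own figure.** The binomial variances are 0.15 × 0.85 = 0.1275 and 0.10 × 0.90 = 0.09. The distance from the expected difference (−0.05) to the margin (+0.05) is 0.10.

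n = (1.645 + 1.282)² × (0.1275 + 0.09) / 0.10² = 186.3, rounded up to 187. The figure reproduces, with no allowance for clustering in it.

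**Step 2: design effects.** DE = 1 + (m − 1) × ICC. At ICC 0.01, DE is 1 + 61.3 × 0.01 = 1.61 (early) and 1 + 45.75 × 0.01 = 1.46 (delayed). The effective sizes are about 116 and 128.

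**Step 3: error rate of an unadjusted interval.** At the margin the rates are 20% and 15%, with variances 0.16 and 0.1275.
- SE assuming independence = √[(0.16 + 0.1275)/187] = 0.0392.
- True SE at ICC 0.01 = √[(0.16 × 1.613 + 0.1275 × 1.458)/187] = 0.0487.
- False non-inferiority = Φ(−1.645 × 0.0392/0.0487) = 9.3%.

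**Step 4: power at 10% v 15%.**
- SE assuming independence = √(0.2175/187) = 0.0341.
- True SE at ICC 0.01 = √[(0.09 × 1.613 + 0.1275 × 1.458)/187] = 0.0421.
- Unadjusted interval: Φ[(0.10 − 1.645 × 0.0341)/0.0421] = 85%.
- Cluster-adjusted interval: Φ(0.10/0.0421 − 1.645) = 77%. A noncentral t on 7 − 2 = 5 df gives 65%.

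| Assumed ICC | False non-inferiority, unadjusted | Power, unadjusted | Power, adjusted (normal) | Power, adjusted (t, 5 df) |
|---|---|---|---|---|
| 0 | 5.0% | 90% | 90% | 81% |
| 0.005 | 7.2% | 87% | 83% | 72% |
| 0.01 | 9.3% | 85% | 77% | 65% |
| 0.02 | 12.7% | 82% | 66% | 55% |
| 0.05 | 19.7% | 75% | 46% | 38% |

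For scale, around a 15% rate the between-hospital standard deviation is √(ICC × 0.1275): about 2.5 percentage points at ICC 0.005 and 3.6 at 0.01.

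**Step 5: simulation.** Beta-binomial data (100,000 runs per scenario, hospitals of 63, 62 and 62 v 47, 47, 47 and 46) gave unadjusted error of 9.6%, 13.1% and 20.4% at ICC 0.01, 0.02 and 0.05, in line with the table.

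**Step 6: would the ICC check catch it?** The article names no test, so a 5%-level chi-square test of heterogeneity within schools (5 df) stands in for it. It flagged ICC 0.01 in about 20% of simulated studies, 0.02 in about 36% and 0.05 in about 70%. Among studies that it did not flag, false non-inferiority stayed at 9.6%, 13.1% and 20.4%.

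**The case against.** The protocol does not ignore clustering. It plans a check and a multilevel model, and it gives reasons to expect little variation: level 2 centers with similar volumes, staffing and perioperative care (5.2.1, 5.8.1) and shared transfusion guidance (5.5.1). If the ICC is zero, the planned interval is right. Section 5.8.1 also names no variance method for the risk difference, and an analysis plan that is not shown might supply one. Allocation is not purely by hospital either, given the mixed protocol and possible surgeon-level switching.

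Much of this is fair, and it limits the claim. But similarity of centers is an expectation, and 5.5.1 itself allows for minor differences in transfusion policy. The mixed hospital and policy switches do not make patients independent. The criticism also rests on what the article does fix: a conditional remedy that is confined to the logistic model.

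Three stronger readings are tempting, and the documents do not support them.
- A reader might take the adjusted powers (83% down to 46%) as the power of the planned analysis. They belong to a cluster-adjusted interval. An unadjusted interval has 87% down to 75%, bought with an inflated error rate.
- A reader might infer that the ICC check can never find clustering that matters. It is weak at 0.02 and below, but it would flag 0.05 in about 70% of studies.
- A reader might infer that the 5% and 90% are certainly lost. That requires an ICC above zero, which the article neither states nor rules out.

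**Conclusion.** The point holds, conditional on some between-hospital variation. The 187 per group contains no clustering allowance, and the stated remedy does not reach the deciding interval whichever way the check falls. Left unadjusted, that interval has a false non-inferiority rate of about 7% to 13% for ICCs of 0.005 to 0.02, and about 20% at 0.05. Adjusting it restores the error rate but brings power below 90%.

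The direction is firm. The size is not, because it rests on assumed ICCs and equal hospital sizes within schools. Unequal sizes would generally make the loss larger. The mixed hospital and policy switches are outside the calculation.

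**What to change.** In 5.8.1, remove the condition that clustering must first be detected. State that the interval for the primary risk difference always accounts for hospital: a marginal risk-difference model with small-sample-corrected cluster-robust variance and a t reference with few-cluster degrees of freedom. Simple hospital-level summaries on 5 df do not fit, because the mixed-protocol hospital, or one that changes policy, can contribute to both timings. The marginal model accommodates this. The ICC can still be reported descriptively.

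In 5.7, state that 187 per group assumes independent patients, and replace the unqualified 90% with power over a stated ICC range.

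The change costs wording and one analysis specification, with no extra patients. The price is a wider interval and a lower stated power, even if the ICC is zero (about 81% with t on 5 df). This accepts the loss of power and does not restore it. With the hospitals fixed at three and four and normal quantiles, 90% would need about 253 per group at ICC 0.005 and 393 at 0.01. It is out of reach at any number of patients above an ICC of about 0.019, because the hospital part of the variance, ICC × (0.09/3 + 0.1275/4), then exceeds the permitted (0.10/2.927)² = 0.00117. The interval should be fixed before outcomes are analysed, so that its choice does not depend on the data.
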